### Intervention

The planned exergame intervention for the experimental group will be carried out using the XBOX Kinect. This device is able to project the player and his or her movements on the screen by means of a camera. It therefore offers the possibility of immersing oneself directly in all sorts of different virtual worlds. The level of physical activity can be increased playfully, and a continuous adjustment to the corresponding level of performance allows the executive functions to be trained. A physically demanding exergame with a strong cognitive component is “Shape UP” (Ubisoft, Montreal, Canada). It is available as a commercial game and resorts to various different elements of endurance, strength and mobility, as well as coordination, working memory, inhibition, attention, speed of action and action planning. In an initial pilot study involving school children, acute effects on cognitive flexibility were noted [62]. In order to achieve the highest possible performance, the player must train both physically and cognitively. The game is designed to be adaptive, automatically adjusting to the player’s level of proficiency. Within the game, there are several different “workouts”, which subjects are supposed to carry out three times a week for at least 30 min, over a period of 8 weeks. The first exergaming session will be conducted under the supervision of the researcher, and at the same time, the intervention will be explained to the children. The parents will be asked to assist and support the children in carrying it out. They too will be given an introduction and brief instructions as to how the game is played. The children and their parents will be informed that they are welcome to contact the study coordinator at any time if they need information or assistance.

### Outcome measures and time-points of assessment

The study is divided up into five phases (T1-T5). These are discussed in chronological order below (see Fig. 1):Baseline (T1): At the beginning of the study, the participants will be fitted with an accelerometer (Actigraph GT9X), which they are expected to wear during the entire study, to monitor their *physical activity level*. By measuring the acceleration in three-dimensional space, it is for example possible to calculate step counts and MET levels. Participants will be asked to wear the devices at night too, if possible, to obtain data on sleep duration.Pre-intervention measurement (T2): The executive functions, sport motor performance, ADHD symptoms, quality of life and background variables will be measured 7 days after handing over the accelerometer. The measures used to determine the *executive functions:* working memory, cognitive flexibility and inhibition, are based on three standardised tests. They are specifically designed for the age group in question and have proven their age adequacy and sensitivity to changes in executive function performance in previous studies [e.g. 51, 65]: working memory performance will be measured using the colour span backwards [66], in which the number of correct answers will be rated. Cognitive flexibility and inhibition will be measured using the adapted Flanker Test [65, 67, 68], again by computer-assisted means. In this, the scores for accuracy and reaction time will be determined. In addition, an adapted version of the Simon Task [69] will be used. The tests have already been successfully used in several studies [51, 65, 70] and proved to be sensitive enough to detect both acute and chronic effects in children between the ages of 8 and 12 years. The cognitive test battery will last approx. 20 min overall. *Sport motor performance* will be measured using the German Motor Test Battery 6–18, which includes eight test items measuring endurance and coordination [71]. Beyond this, the German version of the Physical Activity Enjoyment Scale will be used to measure the subjective pleasure in physical activity [72]. The Shuttle-run Test [73] will be used to measure physical fitness. The *ADHD symptoms* will be ascertained using the German version [74] of the Conners-3 Scales on Attention and Behaviour [75]. These will be completed by parents and teachers. *Quality of life* will be measured using the Inventory of Quality of Life in Children and Adolescents [76]. This questionnaire will be completed by parents and teachers. The *background variables* will be determined using questionnaires and will include the following: age, sex, height, weight, socioeconomic status [77], exercise behaviour [78], and pubertal development [79], completed by the parents.Intervention phase (T3): The children in the experimental group will train three times a week for approx. 30 min over a period of 8 weeks. The frequency of training and the accuracy will be recorded by the XBOX Kinect and using a Training Diary. In addition, the exercise activity will be recorded by an accelerometer (over a period of 8 weeks) and the heart rate will be recorded by a cardio belt (only during intervention sessions).Post-intervention measurement (T4) and follow-up (T5)*:* At these two times (immediately after the conclusion of the study, and again four weeks later) the tests and questionnaires on the executive functions, quality of life, sport motor performance, attention and behaviour used at T2 will be performed once again.

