### Randomisation and blinding

Participants will be randomly assigned to either the intervention or the control group. The randomisation will be conducted in accordance with the regulations of the ethics committee. The teachers will be blinded with respect to treatment allocation, to ensure the data is objective. It will not be possible to blind the researchers and parents since they have to provide guidance on the intervention. Assessments will be performed by two examiners, but as most of the assessments used are objective, the risk of the researcher imposing a bias is small.

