### Trial status

Recruitment for the trial started in March 2016 and is estimated to be completed by June 2017.

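### The blinded teacher ratings fall due on child-specific dates in a recruitment period that spans a summer, so some may be missing or come from a different teacher, at a cost in precision

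*Protocol article*

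**What the plan says.** All places are in the protocol article.

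- **Raters.** Under Outcome measures and time-points of assessment, the article says of the Conners-3 scales: "These will be completed by parents and teachers". Of the quality-of-life inventory it says: "This questionnaire will be completed by parents and teachers".
- **Timing.** The same section ties visits to the child's own start. The T2 measures "will be measured 7 days after handing over the accelerometer". Training then lasts 8 weeks. T4 and T5 come "immediately after the conclusion of the study, and again four weeks later", and at both "the tests and questionnaires on the executive functions, quality of life, sport motor performance, attention and behaviour used at T2 will be performed once again". Counting from T1, T2 is at week 1, T4 at about week 9 and T5 at about week 13.
- **Blinding.** Randomisation and blinding states: "The teachers will be blinded with respect to treatment allocation, to ensure the data is objective". Parents and researchers are not blinded.
- **Calendar.** Trial status states: "Recruitment for the trial started in March 2016 and is estimated to be completed by June 2017".
- **Analysis.** Data analysis plans repeated-measures ANOVAs for primary and secondary outcomes, if applicable, or ANCOVA with the pre-intervention score as covariate. ADHD symptoms and quality of life are secondary outcomes (Study aims and hypotheses).

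Study design gives nine weeks as each child's total time in the study, while T5 falls at about week 13. The two statements need reconciling. The results below are therefore given with T4 and with T5 as the last visit.

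**The concern.** A teacher can rate current behaviour only while teaching the child. The recruitment period contains the whole summer of 2016 and runs up to that of 2017. A child who starts in late spring or early summer may have a visit during the break, so that the teacher form is late or missing. Such a child may also have visits on either side of a new school year, so that a different teacher may complete the later form.

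A conventional repeated-measures ANOVA drops a child with a missing visit. It also counts a change of teacher as change in the child. In a trial with a passive waiting-list control and unblinded parents, the teacher forms are the only blinded evidence on these two outcomes. If they thin out, the conclusions rest more heavily on the parents.

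**Working it through.** **1. The plan's own sample size.** Inputs from Participants: 2 groups, 3 measurements, correlation .8, power .80, small effect. I take small as f = .10 and alpha as .05.

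λ = f² × N × m / (1 − ρ) = 0.01 × 66 × 3 / 0.2 = 9.9, with 2 and 2 × (66 − 2) = 128 degrees of freedom. The noncentral F gives power .802, and 66 is the smallest even N that reaches .80. The figure reproduces, and it contains no allowance for lost ratings.

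**2. Share of schedules that meet the summer.** Assumptions: T1 is spread evenly over 1 March 2016 to 30 June 2017 (306 + 181 = 487 days). The break starts on 1 or 8 July and lasts L days, from 28 (4 weeks) to 49 (7 weeks). Other holidays are ignored.

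Let S be the days from T2 to the last visit (56 for T4, 84 for T5). For the full summer of 2016, S + L start dates give a schedule that has a visit in the break or spans it. For 2017, the last T2 is 7 July (30 June + 7 days). That leaves S start dates if the break begins on 8 July, or S + 7 if it begins on 1 July.

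| Schedule | 4 weeks from 8 July | 7 weeks from 1 July |
|---|---|---|
| T2-T4 | (56 + 28) + 56 = 140; 140/487 = 28.7% | (56 + 49) + 63 = 168; 168/487 = 34.5% |
| T2-T5 | (84 + 28) + 84 = 196; 196/487 = 40.2% | (84 + 49) + 91 = 224; 224/487 = 46.0% |

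**3. Separating the two problems.** A second count uses entry from 14 March 2016 (the registration date) to 30 June 2017, which is 474 days, and a five-week break from 9 July. The two categories overlap.

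| Schedule | A visit in the break | Crosses into new school year | Either |
|---|---|---|---|
| T2-T4 | 22% | 16% | 31% |
| T2-T5 | 34% | 28% | 43% |

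**4. Sensitivity, same five-week break, T2-T5 unless stated.**

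- Only one third of crossing children change teacher: 37% (25% for T2-T4).
- Forms can also move by 14 days. Only the middle 7 days of the break then remain a problem for each visit: three visits in 2016 and two in 2017, so 5 × 7 = 35 days and 35/474 = 7.4%. This is the share if no child changes teacher.
- Forms can move by 14 days and one third change teacher: 0.074 + 0.33 × (0.308 − 0.074) = 15.1%. Here 0.308 is the share if every crossing child changes teacher.
- June 2017 is the last T5 rather than the last entry: 29-33% for breaks of 4 to 6 weeks, falling to 7-16% with 14-day movement and one-third teacher change.
- No starts from 7 April to 15 August: 0%.

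The 7% and 15% figures depend on the length of the break. With no teacher change they are 0% for four weeks and 14.8% for six. With one-third change they are 0.33 × 0.293 = 9.7% and 0.148 + 0.33 × (0.323 − 0.148) = 20.6%.

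**5. What lost ratings would cost, as illustration only.** With the inputs of step 1 and complete cases, a 10% loss (N = 59) gives power .75, 20% (N = 53) gives .70 and 30% (N = 46) gives .63. The article does not state these inputs for the teacher-rated outcomes, so the figures show a gradient and are not a forecast.

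**The case against.** The strongest objection is that a journal article condenses the full protocol. Visit windows, term-time scheduling, continuity of raters and missing-data rules may stand in documents that are not shown. No sentence here contradicts another on this point. The article does not say that entry is even or that T1 follows recruitment at once, and starts could be grouped around the school year. All of this stands, so the silence is not treated as an error. What remains is that the stated visit timing and recruitment period, followed as written with even entry, put teacher forms out of term.

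A reader might infer more, in four ways that the article does not support:

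- *That the blinded outcome cannot be scored for these children.* A form may only be late, a new school year need not bring a new teacher, and parents complete the same scales.
- *That 30-46% of children are lost and power falls accordingly.* Those shares include children who only cross a school year and still have ratings. Nor can a lower correlation be applied to all 66 children: with 28% crossing and one third changing teacher, about 9% are affected (0.28 × 0.33).
- *That the result is biased in one direction.* The loss follows start date, and with concurrent randomisation it should affect both arms alike.
- *That the primary outcome is at risk.* The executive-function tests need no teacher.

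**Conclusion.** The point holds as a matter of precision on two secondary outcomes. Given roughly even entry and a summer break of 4 to 7 weeks, about 29-35% of T2-T4 schedules and 40-46% of T2-T5 schedules touch the break or cross a school year. The documents give no break dates, entry pattern or teacher-change rate, so these figures are conditional. With a five-week break the share falls to about 7-15% if forms can move by two weeks and few children change teacher, and to 0% if starts avoid the summer. Some blinded ratings would be missing or made by another teacher. How many cannot be fixed from the article.

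**What to change.** For children still to be enrolled:

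1. Time T1 where possible so that at least T2 and T4 fall in school weeks of the same school year. Allow a short stated window for teacher forms.
2. Have the same teacher rate a child at each visit where possible, and record who rated and when.

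For the analysis of teacher ratings:

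3. Replace a complete-case repeated-measures ANOVA with a mixed model that keeps children with a missing visit.
4. Keep ratings by a new teacher, flagged, in the main analysis. They are still blinded and still compare the randomised arms.
5. Add a sensitivity analysis restricted to same-teacher ratings.

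This needs a few sentences and one extra field on the form, with no additional children or procedures. The price is that some children start later, so data collection may end a few months later.

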
**Fig. 1 Fig1:**
[figure not shown]
Outcome variables and time points of assessments. CG = Control Group; EG = Experimental Group

### Randomisation and blinding

Participants will be randomly assigned to either the intervention or the control group. The randomisation will be conducted in accordance with the regulations of the ethics committee. The teachers will be blinded with respect to treatment allocation, to ensure the data is objective. It will not be possible to blind the researchers and parents since they have to provide guidance on the intervention. Assessments will be performed by two examiners, but as most of the assessments used are objective, the risk of the researcher imposing a bias is small.

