**Methods:**

The aim of the study is to examine the effects of a cognitively and physically demanding exergame on executive functions of children with ADHD. In a randomised clinical trial, 66 girls and boys diagnosed with ADHD (age 8–12) will be assigned either to an 8-week exergame intervention group (three training sessions per week à 30 min) or a waiting-list control group. Before and afterwards, the executive function performance (computer-based tests), the sport motor performance and ADHD symptoms will be assessed.

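### The two examiners are not separated from the unblinded role of guiding the intervention, and calling the tests objective does not cover encouragement, mainly in the motor testing

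*Protocol article*

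**What the plan says.** The relevant text is in the protocol article, mostly under Randomisation and blinding.

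- Researchers and parents: "It will not be possible to blind the researchers and parents since they have to provide guidance on the intervention".
- Examiners: "Assessments will be performed by two examiners, but as most of the assessments used are objective, the risk of the researcher imposing a bias" is described as small.
- Teachers are the only group declared blinded: "The teachers will be blinded with respect to treatment allocation, to ensure the data is objective". Under Outcome measures and time-points of assessment, teachers complete the Conners-3 and quality-of-life questionnaires. They do not supply the performance tests.
- Contact with the intervention arm (Intervention section): "The first exergaming session will be conducted under the supervision of the researcher". The same section names a study coordinator whom families may contact for help.
- The tests: the abstract says "the executive function performance (computer-based tests), the sport motor performance and ADHD symptoms will be assessed". For the Flanker test, "In this, the scores for accuracy and reaction time will be determined". The motor battery is one "which includes eight test items measuring endurance and coordination". A shuttle run measures physical fitness.
- T4 and T5 repeat the T2 measures of executive functions, quality of life, sport motor performance, attention and behaviour. Physical fitness is not named in that list.

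The control group is a passive waiting list (Study design). The limitations in the Discussion do not mention examiner blinding.

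**The concern.** The reassurance rests on two steps, and neither holds fully.

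First, the reason given for not blinding is that researchers have to guide the intervention. That reason applies only to people who give guidance. It does not apply to an examiner who gives none, and two examiners are already planned.

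Second, objectivity of a test protects the recording of the result. It does not protect what happens before the result is recorded: how the task is explained and how hard the child is urged on. Endurance items depend heavily on effort. An examiner who knows the allocation can, without intending it, encourage children in the exergame arm more.

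Sport motor performance is the first secondary outcome under Study aims and hypotheses. The trial looks for small effects, so even a modest systematic difference between arms in the testing sessions would count.

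**Working it through.** **1. The statements side by side**

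| Question | What the article says |
|---|---|
| Who is unblinded? | Researchers and parents, because they guide the intervention |
| Who is blinded? | Teachers only |
| Who tests the children? | Two examiners, blinding not stated |
| Are examiners separate from those who guide? | Not stated; the same sentence moves from examiners to the researcher |
| Why is the bias risk called small? | Most assessments are objective |

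Nothing in the plan as written would keep the allocation from the person who tests at T4 and T5.

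**2. Reproducing the plan's sample size**

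Inputs from the Participants section: two groups (k = 2), three measurements (m = 3), correlation ρ = 0.8, power 0.80, a small effect. From Data analysis: α = 0.05. The effect size is not given as a number, so f = 0.10 is assumed.

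- λ = f² · N · m / (1 − ρ) = 0.01 × 66 × 3 / 0.2 = 9.9
- df1 = (k − 1)(m − 1) = 2; df2 = (N − k)(m − 1) = 64 × 2 = 128
- Power from the noncentral F: 0.8015 at N = 66 and 0.7949 at N = 65

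The smallest N that reaches 0.80 is 66, the stated figure. This supports f = 0.10 as the intended value.

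**3. What f = 0.10 means in SD units**

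Let the arms differ by b SD at T4 and T5 and by 0 at T2. Each arm then deviates by ±(0, b/2, b/2) over time. The sum of squares about the time mean is b²(1/9 + 2/36) = b²/6, so f² = (b²/6)/3 = b²/18. Setting f = 0.10 gives b = 0.1 × √18 ≈ 0.42 SD.

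**4. Assumed examiner shift, no true effect**

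Suppose examiner behaviour alone adds b SD to the exergame arm at T4 and T5, with 33 children per arm (the allocation ratio is not stated).

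- Repeated-measures interaction test (the default analysis): λ = 66 × (b²/6) / 0.2 = 55b², df 2 and 128. For b = 0.1, λ = 0.55; for b = 0.2, λ = 2.2.
- ANCOVA at T4 (the fallback when baseline scores differ significantly): residual SD = √(1 − 0.8²) = 0.6, noncentrality = (b/0.6) × √(33/2). For b = 0.1 this is about 0.68.

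| Assumed shift b (SD) | Interaction test, P(p < .05) | ANCOVA, P(p < .05) |
|---|---|---|
| 0 | 0.050 | 0.050 |
| 0.05 | 0.060 | 0.063 |
| 0.10 | 0.093 | 0.102 |
| 0.15 | 0.152 | 0.170 |
| 0.20 | 0.240 | 0.266 |
| 0.30 | 0.490 | 0.516 |

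A shift of 0.1 SD is 0.1/0.42 ≈ 24% of the assumed design effect. A shift of 0.05 SD would hardly matter.

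**The case against.** - **The examiners may not be the unblinded researchers.** A reader might infer from the article that unblinded researchers do the post-intervention testing. It does not say so. The link comes from one sentence that speaks first of examiners and then of the researcher. The inference is reasonable, because the reassurance would hardly be needed if the examiners were blinded, but it remains an inference. What stands is that the roles are not separated.
- **An article may leave examiner assignment to the full protocol.** That would answer a complaint about missing detail. It does not answer this point, because the article itself gives a reason for not blinding and a reason for calling the risk small, and both are too broad.
- **The primary outcome is well protected.** A reader might infer that the executive-function result is equally exposed. The documents do not support that: these tests are computer-based, standardised and scored by correct answers, accuracy and reaction time. Instruction and motivation may still play some part, but the exposure is much smaller than in motor testing.
- **The shuttle run may not be repeated.** This is correct. The list for T4 and T5 does not name physical fitness, so the point covers the shuttle run only if it is repeated.
- **The size is assumed.** This is also correct. Any assumed bias inflates rejection, so the table shows sensitivity and is no evidence that a bias exists.
- **A waiting list creates expectation effects anyway.** Children and parents know their allocation, and a blinded examiner does not change that. The Discussion already lists the waiting-list control as a limitation.
- **Both examiners may be needed in one session.** The article does not say whether they work together. If they do, the roles cannot be split without further staff.

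**Conclusion.** The point holds in a limited form. The article declares the researchers unblinded for a reason that need not apply to every examiner, does not separate the two examiners from the guiding role, and calls the bias small on an argument that covers scoring but not encouragement. The exposure lies mainly in the motor battery.

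If the true effect is nil, an examiner shift of 0.1 SD would roughly double the false-positive rate of the planned interaction test, to about 9%, and 0.2 SD would bring it to about 24%. This rests on assumed shifts, f = 0.10, ρ = 0.8 and equal arms. It does not show that a bias will occur, and it does not question the sample size, which reproduces. The change is worth making because it is cheap; leaving it undone would not invalidate the primary comparison.

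**What to change.** 1. For each family, let one examiner or the study coordinator introduce the game and support the family. Let the other examiner, who is not told the allocation, test at T4 and T5.
2. Ask families not to mention the game at testing.
3. Use a fixed script for instructions and encouragement in both arms.
4. If both examiners are needed in the same session, keep the script, remove the statement that the risk is small, and list unblinded assessment of motor performance among the limitations.

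The cost is scheduling effort. Sample size, outcomes and analysis stay as they are. Some children will reveal their allocation, so blinding will be incomplete, and expectation effects among children and parents will remain.
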